**Figure 1 fig1:**
[figure not shown]
Flowchart of the study.

**Table 1 tab1:** Overview of all measures and their assessment times.

Measure	Target	Baseline	Every 2 months follow-up-	Every 6 months follow-up	2.5 years follow-up
Demographics	Sociodemographic data	X			X
CUDIT-R	Problematic cannabis use	X		X	X
CS-CCU*	Cannabis use patterns	X	X	X	X
LRCU*	Lower-risk cannabis use	X		X	X
Motives*	Cannabis use motives	X		X	X
PANAS	Positive and negative affect	X	X	X	X
PHQ-9	Depression	X		X	X
GAD-7	Anxiety	X		X	X
ASRS-V1.1	Attention deficit and hyperactivity	X		X	X
ERIRaos	Psychosis	X		X	X
SCL-90 Somatization	Physical symptoms	X		X	X
CAT	Respiratory symptoms	X		X	X
EuroQol-5D	Quality of life	X		X	X
SAE*	Serious adverse events	X	X	X	X
PSQI	Sleep	X		X	X
GLTEQ	Physical activity	X		X	X
AUDIT-C	Alcohol use	X		X	X
ASSIST	Illicit substance use	X		X	X
S-CNU*	Nicotine use	X		X	X
Drugs	Drug use	X		X	X
Blood sample	Epigenetic analysis	X			

* These are no official instruments. These questionnaires were developed in cooperation with scientific partners from the universities of Basel, Bern, Geneva, Lausanne, St. Gallen and Zürich as well as the Swiss Federal Office of Public Health as a common basis for data collection of the pilot trials in Switzerland.

ASRS-V1.1 Adult ADHD Self-Report Scale, ASSIST Alcohol, Smoking and Substance Involvement Screening Test, AUDIT-C Alcohol Use Disorders Identification Test, CAT COPD Assessment Test, CS-CCU Comprehensive Short Questionnaire of Current Cannabis Use, CUDIT-R Cannabis Use Disorders Identification Test—Revised, EuroQol-5D European Quality of Life, ERIraos Early Recognition Inventory Checklist, GAD-7 Generalized Anxiety Disorder, GLTEQ Godin Leisure Time Exercise Questionnaire, LRCU Lower-Risk Cannabis Use, PANAS Positive Affect and Negative Affect Scale, PHQ-9 Patient Health Questionnaire, PSQI Pittsburgh Sleep Quality Index, SAE Serious Adverse Events, SCL-90 Somatization Symptom Checklist-90, S-CNU Short Questionnaire of Current Nicotine Use.

### Interventions

Eligible participants are randomized in equal proportions between the experimental and the control group. The experimental group has access to regulated cannabis in nine pharmacies that have been previously selected. The control group will have access to regulated cannabis with 6-month delay. After these 6 months, both groups will have access to cannabis in pharmacies for the following two years. Several potential conditions are available to facilitate lower-risk cannabis use and treatment within the intervention of cannabis regulation (60, 61).

Product quality: Participants are provided high quality cannabis products without any contamination and with declared THC/Cannabidiol (CBD) content. Participants can choose between six different cannabis products that are produced by a Swiss cannabis company: Four flower products and two hash products with different THC and CBD ratios.Regulated access: THC content is limited to a maximum of 20% THC. Additionally, the cannabis amount that participants can buy per month is limited to up to 10 g of total THC per month (participants can buy more of a product with low THC content compared to a product with high THC content).Pricing: Prices of the cannabis products in pharmacies are comparable to the products on the illicit market, so they do not compete. In order to promote lower-risk products, products with higher THC content are more expensive than products with lower THC content.Protection of minors: Only persons older than 18 years are allowed to participate in the study.

Facilitated access to users:

Prevention: Pharmacists inform participants about lower-risk use guidelines such as products with lower THC content or vaporizers (62, 63). Furthermore, health prevention information and lower-risk use guidelines will be also available on the product packaging as well as on the study website.Early detection, early intervention, and encouraging treatment: Pharmacists may notice any potential health risks in participants. In this case, pharmacists will conduct a brief intervention and will recommend to contact the study physician, a local counseling or treatment institution. In case of a severe health risk, pharmacists may impose a consultation with the study physician. He will check whether legal cannabis access is still medically acceptable for this participant. The study physician trained all pharmacists on lower-risk cannabis guidelines as well as on red flags of cannabis use disorder, psychosis, depression, and suicidality. Besides the pharmacists, cannabis use disorder, depression, anxiety, and psychosis will be assessed every 6 months *via* online-assessments. If participants show a significant deterioration in one of these aspects, the study physician will contact the affected participant, will evaluate whether cannabis access remains medically responsible, and will provide treatment options.

The control group shall display the status quo in Switzerland, namely the situation of the illicit market. Therefore, during the first 6 months, the waiting list control group has no access to cannabis in pharmacies. They have to continue to obtain their cannabis *via* their usual sources. Additionally, any prevention information and early detection and intervention in pharmacies are lapsed for this group during the first 6 months.

### Outcomes

Table 1 provides an overview of all measures and time points when they are assessed in the study. All questionnaires are administered in German and all available German versions of questionnaires are used. Additionally, all measurements are self-reported and assessed online.

#### Primary outcome

The present study evaluates whether regulated cannabis access improves problematic cannabis use. The primary outcome is the difference of problematic cannabis use between the two groups after 6 months. Problematic cannabis use will be assessed by the “Cannabis Use Disorders Identification Test-Revised (CUDIT-R)” (64). The scale includes eight statements about cannabis use with answers ranging from “never” (0) to “daily or almost daily” (4). The total score ranges from 0 to 32 with scores of 13 and more indicating a possible cannabis use disorder. Problematic cannabis use assessed with CUDIT-R could be reduced after 6 months (65). In order to detect a change in cannabis use as well as to keep the waiting period for the control group as short as possible, the trial period is set at 6 months.

#### Secondary outcomes

##### Cannabis use patterns

The *Comprehensive Short Questionnaire of Current Cannabis Use* (CS-CCU) evaluates cannabis use patterns during the last 30 days. The questionnaire includes 23 questions about cannabis quantity used, frequency, products, and mode of administration. Moreover, participants will be asked whether they continue to obtain illegal cannabis. Specifically, the amount of illegal cannabis and the frequency of its use during the last 30 days are assessed. In addition, participants’ satisfaction of the regulated cannabis access will be assessed (e.g., products, pharmacies, and information provided).*Cannabis consumption motives* are assessed with ten items covering a range of motives such as “to relax,” “to reduce physical symptoms,” and “to enhance concentration.” Ten statements will be rated on a 5 point-Likert scale from “never/almost never” (0) to “almost always/always” (4).To assess knowledge and behavior of safer cannabis use guidelines, the scale *Lower-Risk Cannabis Use–Knowledge and Behavior* is used. This measure includes 24 statements that must be answered on a 4 point-Likert scale that ranges from 0 to 4. The total score ranges from 0 to 48 with higher scores indicating more knowledge and behavior of lower-risk cannabis use.

Additional objective data on cannabis purchased are collected in pharmacies. These data include type of products (THC- and CBD-content) purchased and quantity purchased per month.

##### Mental health

The *Patient Health Questionnaire for Depression (PHQ-9)* includes nine items that assess the degree of depression. Answers range from “not at all” (0) to “almost daily” (3) with a total score between 0 and 27. A score of 10 or higher is considered indicative of a major depressive disorder (66, 67).The *Generalized Anxiety Disorder Scale-7 (GAD-7)* is an instrument that consists of seven items on anxiety symptoms with answers ranging from “not at all” (0) to “almost daily” (3) (68). The total scores are between 0 and 21 and scores of 10 or above are considered indicative of a generalized anxiety disorder (69). GAD-7 showed to be a valid and reliable measure for anxiety (69).The *Adult-ADHD Self-Report Scale (ASRS-V1.1)* is a six-item questionnaire on attention deficit and hyperactivity disorder (ADHD) with answers ranging from “never” to “very often.” Total scores of four or above are considered indicating a positive screening result of ADHD (70).The Early Recognition Inventory (ERIraos) Checklist is a screening instrument for the early recognition of psychosis risk (71). We only use the items on early psychosis including eight statements that are answered with “no” (0) / “yes” (1). Scores of one ore higher are considered as indicative for an early psychosis.The *Positive and Negative Affect Schedule (PANAS)* is a scale to assess positive and negative effects in the last days, that addresses affective states (72, 73). The measure includes 20 items that are rated on a 5 point-Likert scale ranging from “very slightly or not at all” (1) to “extremely” (5). Mean score of each dimension (positive and negative affect) indicates a higher positive and negative affective state, respectively.

##### Physical health

The *EuroQuol-5D* contains five dimensions of health-related quality of life (morbidity, self-care, daily activities, pain/discomfort, and depression/anxiety) rated on a scale ranging from “no problems” (0) to “extreme problems” (5). Furthermore, participants’ health status is assessed by a single index measure ranging from 0 to 100 (74). The total score of the five dimensions is used as a measure of quality of life.Physical symptoms are assessed with the dimension *Somatization* of the *Symptom Checklist-90 (SCL-90)* (75). This subscale consists of 12 items that are scored on a 5 point-Likert scale ranging from “not at all” (1) to “extremely” (5). The total score ranges from 12 to 60 and higher scores indicate higher physical discomfort.Respiratory symptoms are evaluated with the *COPD Assessment Test (CAT)*. This is an eight-item scale covering all aspects of chronic obstructive pulmonary disease (COPD) and indicates the severity of COPD. Each item is formatted as a semantic six-point differential scale. Higher total score indicates worse respiratory health status (76).*Serious adverse events* are assessed with two items asking participants whether they were hospitalized longer than 24 h and whether they experienced a life-threatening event since the last survey.

##### Consumption of other substances

The *Alcohol Use Disorders Identification Test-Consumption (AUDIT-C)* is a screening tool including three items that assess problematic and risky alcohol use. The questions are answered on a 5 point-Likert scale ranging from 0 to 4 with a total score between 0 and 12. Scores of 2 or above in women and of 4 or above in men are considered as indicative for alcohol misuse (77).The *Alcohol, Smoking and Substance Involvement Screening Test (ASSIST)* is an instrument that assesses drug consumption with answers ranging from “never” (0) to “daily or almost daily” (4) (78). We only use the pre-screener question without the items on tobacco and alcohol and with an adapted time frame to 6 months instead of 3 months.The *Short Questionnaire of Current Nicotine Use (S-CNU)* includes nine items about current nicotine use. Additionally, the two items of Heaviness of Smoking Index are included (79). In total, the instrument consists of 11 items.*Medication use* is assessed with a ten-item scale covering ten medications with answers ranging from “never” (0) to “almost daily/daily” (4).

##### Health behaviors

Sleep is measured with the two items from the *Pittsburgh Sleep Quality Index* that have been shown the highest correlation between single-item and the final score of the full scale (single-item—total correlation), *r* = 0.83 for sleep quality and *r* = 0.80 for sleep duration (80). Participants rate their sleep quality on a 4point-Likert scale from “very bad” (1) to “very good” (4) and indicate the hours of actual sleep.Physical activity is evaluated with the *Godin Leisure Time Exercise Questionnaire.* Participants will be instructed to indicate the number of minutes engaged in mild, moderate, and strenuous exercise during the last week. The minutes of mild, moderate, and strenuous exercise are weighted by metabolic equivalents and then summed to produce a total weekly leisure activity score. Higher scores reflect higher levels of physical activity (81).

Besides the current study, further studies on cannabis regulation in Switzerland are planned in order to gain insights into different regulation models and its impact on health, cannabis use, and safety, among others. The Swiss Federal Office of Public Health is interested in conducting analyses over all these studies in order to provide a more broadly evidence-based information for policymakers. Therefore, the aim is that these studies include a minimum set of the same questionnaires that allows to compare the data of the various studies. This set of questionnaires was developed by researchers of several Swiss universities that are involved in these studies and the Swiss Federal Office of Public Health. This set includes questionnaires about cannabis use patterns, problematic cannabis use, mental and physical health, and consumption of other substances. These questionnaires are also included in the present study.

##### Epigenetic analysis

At baseline, a blood sample will be collected from participants for analysis of epigenetic gene express regulation. DNA methylation of genes regulating the HPA (POMC, and NR3C1) as well as neurotrophic growth factors (BDNF, GDNF, NGF, and VEGF-A) will be investigated.

### Sample size

The sample size was calculated on the basis of the primary hypothesis. A reliable change in problematic cannabis use is defined as a change of two points or greater in mean CUDIT-R after 6 months (65). The power analysis (power of 0.8, alpha of 0.05, dropout of 20%) identified a target enrollment of 374 cannabis users—187 per group—to detect a reliable change in problematic cannabis use after 6 months.

### Statistical methods

Descriptive statistics will be reported for sociodemographic and baseline characteristics. For the analysis of the primary outcome, analysis of covariance will be used (82). This model includes CUDIT-R mean after 6 months as dependent variable and the study group (experimental, control group) and the CUDIT-R mean at baseline as independent variable. Linear mixed models will be conducted for the analyses of the secondary outcomes in order to evaluate between-person and within-person differences during the 2 years of regulated cannabis access. Additionally, potential effect modification will be analyzed (gender, age, education, and cannabis consumption motives). Data will be analyzed according to the intention-to-treat-principle and thus (82), all patients being enrolled in the study and answered the baseline survey will be included.

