**Methods:**

The study is divided into two parts—a randomized controlled study of 6 months followed by an observational study of 2 years. Participants (*N* = 374) are randomly assigned to either the experimental group with access to legal cannabis in pharmacies or to the waiting list control group representing the current legal framework in Switzerland, namely the illicit market. After 6 months, all participants will have access to legal cannabis for the following 2 years (observational study). The primary outcome is problematic cannabis use as measured with the Cannabis Use Disorders Identification Test-Revised (CUDIT-R). Secondary outcomes are cannabis use patterns, mental disorders (e.g., depression, anxiety, and psychosis) and physical health (e.g., respiratory symptoms). Primary and secondary outcomes will be assessed online every 6 months. The study is approved by the responsible ethics committee as well as by the Swiss Federal Office of Public Health.

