To our knowledge, there is no randomized controlled study evaluating the effects of recreational cannabis legalization compared to the illicit market on relevant health outcomes. Available evidence is based on observational studies, including pre-post-legalization comparisons or comparisons between states with recreational cannabis regulation and states without. However, these study designs are not able to distinguish between secular trends and changes due to cannabis regulation and thus, causality remains unclear (47). The aim of the present randomized controlled study is to investigate the effects of cannabis regulation for recreational purposes compared to the illicit market on problematic cannabis use, mental disorders, and physical health. Although cannabis for recreational use is prohibited in Switzerland, scientific studies on recreational cannabis are allowed since 2021 (48). Hence, Switzerland offers a unique opportunity to gain scientific knowledge about alternative cannabis regulation approaches. We hypothesize that regulated cannabis access in pharmacies will reduce problematic cannabis use as within a regulated approach several conditions are available to facilitate lower-risk use and treatment. Furthermore, we hypothesize that regulated cannabis access will improve mental and physical health outcomes.

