## Methods

### Design

The study “Weed Care” is designed as a randomized, controlled, unblinded superiority trial with two parallel groups. Participants will be randomized to the experimental group with legal cannabis access in pharmacies or to the waiting list control group representing the illicit market. The primary endpoint is 6 months of regulated cannabis access. After 6 months, an observational study of 2 years will follow. During this time, both groups will have access to cannabis in pharmacies. This monocenter study will be conducted in the canton Basel-Stadt in Switzerland. The study has been approved by the local ethics committee “Ethikkommission Nordwest- und Zentralschweiz” (EKNZ) as well as by the Swiss Federal Office of Public Health. Furthermore, the study is designed in agreement with the Declaration of Helsinki, the ICH-GCP guidelines, and the Swiss law, notably the amendment of the Federal Act on Narcotics and Psychotropic Substances. The latter defines certain conditions for scientific studies with recreational cannabis such as minimum age of participants and maximum tetrahydrocannabinol (THC-) content (48).

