In Switzerland, cannabis for recreational use is prohibited, but the Federal Act on Narcotics and Psychotropic Substances allows scientific studies with cannabis since 2021 (48). The aim of this law is to increase evidence-based knowledge of the advantages and disadvantages of different regulatory approaches, and thus, to provide a scientific basis for discussions about future cannabis policy in Switzerland. To our knowledge, the present study “Weed Care” is the first randomized controlled trial that evaluates the effects of recreational cannabis regulation compared to the illicit market on problematic cannabis use as well as on mental and physical health outcomes. This study design will provide compelling evidence elucidating benefits and harms of recreational cannabis regulation on relevant health indicators. For example, if results show that cannabis use and health outcomes improve after 6 months in the group with legal access compared to the control group, policymakers may consider the evaluated type of cannabis regulation to be superior to the prohibition. Besides improved users’ health, an additional benefit might be decreasing health costs in the long-term. However, this is not part of the present study. If results show no difference in health outcomes between the two groups, the analyzed regulation model is not inferior to prohibition and may still display a potential alternative approach for drug policy since prohibition has not achieved its aims over the last decades. In contrast, if results show that cannabis use and health outcomes deteriorate in the group with legal cannabis access compared to the control group, policymakers may draw the conclusion that these results favors cannabis prohibition. However, all conclusions should be drawn with caution, since the present study investigates one potential regulation model and its effect on health outcomes. Further research is needed to investigate the effects of regulated cannabis on additional outcomes such as on youth, criminality, stigmatization, or illicit market. Moreover, the evaluation of other regulation models such as cannabis social clubs or cannabis shops is substantial in order to compare the benefits and harms of different regulation approaches.

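### The only analysis stated for the secondary outcomes covers the two years when both arms have legal access, and no analysis is assigned to the randomised month-6 comparison that the health hypothesis needs

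*Protocol article*

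**What the plan says.** **Analysis.** In Statistical methods, the primary outcome has an analysis of covariance: CUDIT-R at 6 months on study group and baseline CUDIT-R. For the secondary outcomes the section names linear mixed models, with this purpose: "in order to evaluate between-person and within-person differences during the 2 years of regulated cannabis access". It adds effect-modification analyses and an intention-to-treat statement. No month-6 group comparison of a secondary outcome is stated.

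**Design.** The abstract describes "a randomized controlled study of 6 months followed by an observational study of 2 years". On the second part, the Design section says "During this time, both groups will have access to cannabis in pharmacies", and Interventions repeats it: "After these 6 months, both groups will have access to cannabis in pharmacies for the following two years". Interventions confines the no-access control condition to the first 6 months.

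**Question.** The aim in the Introduction is a comparison with the illicit market that covers mental disorders and physical health as well as problematic use. It continues: "Furthermore, we hypothesize that regulated cannabis access will improve mental and physical health outcomes". The Discussion's leading scenario is that "cannabis use and health outcomes improve after 6 months in the group with legal access compared to the control group", and it attaches a policy reading to that result, to no difference, and to deterioration.

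**The concern.** The window named for the secondary analysis is one in which the comparator in the aim no longer exists. An analysis plan that followed the article to the letter would describe two years of trajectories under access and would not test the health hypothesis. A plan that did test it, at month 6, would depart from the published text. Window and contrast would then be chosen across many secondary scales after publication, which invites a charge of selection.

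The open phase is no substitute. Within-person change there combines any effect of access with secular trend, regression to the mean and differential loss to follow-up. The Introduction makes a related criticism of the existing literature, saying that "these study designs are not able to distinguish between secular trends and changes due to cannabis regulation". It is aimed at before-after and between-state studies of legalisation, but the reasoning carries over to within-person change without a concurrent unexposed group.

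**Working it through.** The claim concerns which visits carry the legal-versus-illicit contrast, so the main check sets access status against the visit schedule.

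**Inputs.**
- Full assessments at baseline and at 6, 12, 18, 24 and 30 months (Participant timeline).
- The experimental arm has access from the start, and the control arm 6 months later (Interventions).
- The mental-health, somatic, respiratory and quality-of-life scales are collected at baseline and every 6 months (Table 1).

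**Access by visit.** Months are nominal, ignoring the two weeks between the baseline survey and the opening of access.

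| Visit (month) | Months of access, experimental | Months of access, control | Does the control arm represent the illicit market up to this visit? |
|---|---|---|---|
| 0 | 0 | 0 | neither arm has access yet |
| 6 | 6 | 0 | yes |
| 12 | 12 | 6 | no |
| 18 | 18 | 12 | no |
| 24 | 24 | 18 | no |
| 30 | 30 | 24 | no |

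From month 12 the difference is always 6 months of earlier access (12 − 6, 18 − 12, 24 − 18, 30 − 24), and both arms have access throughout. A group term in that window answers whether starting 6 months sooner matters later. That differs from asking whether access is better than the illicit market.

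**What remains for the hypothesis.** For scales on the six-monthly schedule, month 6 is the only follow-up that carries the randomised contrast. Affect (PANAS) and cannabis use patterns are also collected at 2 and 4 months, inside the controlled period. The data for the randomised comparison are therefore scheduled, but the text does not assign an analysis to them.

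**What the month-6 contrast could show.** The plan's own figure, 187 per group, belongs to the primary outcome. It cannot be reproduced directly because no SD is given. For a difference of 2 points at two-sided 0.05 (sidedness is not stated) and 80% power, an SD of about 6.16 fits:

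n = 2 × (1.960 + 0.842)² × (6.16 / 2)² ≈ 149 per arm, and 149 / 0.8 = 186.25, rounded up to 187.

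The point does not depend on that SD. Taking the planned 20% dropout, 187 × 0.8 = 149.6, so about 149 per arm are analysable. The detectable standardised difference for a secondary score at month 6 is then

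(1.960 + 0.842) × √(2 / 149) ≈ 0.32 SD,

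before any gain from baseline adjustment.

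**The case against.** The strongest reply is that this is one condensed sentence in a journal article, and that the group term, visit set and contrasts of a mixed model normally sit in the analysis plan. The wording also leaves room. Study group is a between-person factor. The intention-to-treat sentence takes in everyone who answered the baseline survey. Month 6 is the boundary of the two-year phase, where controls have had no pharmacy access. The experimental arm has 2.5 years of access in all, so the two-year phrase may be loose. The Discussion shows that a 6-month comparison is intended.

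Much of this stands, and it rules out a stronger reading. A reader might infer that the trial, or its mixed models, cannot test the health hypothesis. The documents do not support that: a model that includes baseline and month 6 with a group-by-time term would recover the randomised contrast. The text does not state such a model, but neither does it exclude one.

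Three further inferences should be resisted:
- That the group effect will be averaged over all follow-ups and so diluted. No section proposes such averaging.
- That people who miss a questionnaire leave the study. In context, the block in Participant timeline is on buying in pharmacies.
- That regression to the mean can be sized here. The article gives no retest correlation or distance from the mean, and Eligibility criteria set no symptom threshold that would fix its direction for health outcomes.

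The article also already calls the open phase observational.

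What does not stand is the claim that this is merely missing detail. The article goes further than leaving the window open. It names one, and that window conflicts with its own hypothesis and intended reading.

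**Conclusion.** The concern holds as a conflict between the stated secondary analysis and the question it serves. Statistical methods points the secondary models at the phase with access in both arms, while the Introduction and Discussion require a month-6 comparison with the control arm. It affects every secondary outcome behind the mental- and physical-health hypothesis.

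The severity is moderate. The primary ANCOVA of CUDIT-R at 6 months is correctly placed and unaffected, and the secondary data are scheduled. The conclusion rests on reading the two-year phrase as the observational phase, as the abstract, Design and Interventions all use it. No bias is quantified, because the documents give no basis for a figure. The 0.32 SD describes what the month-6 contrast could detect. It assumes 20% dropout in each arm and a two-sided 5% test.

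**What to change.** State in Statistical methods, and carry into the analysis plan, that each secondary outcome behind the health hypothesis is tested by the baseline-adjusted between-group difference at month 6. Either of two forms will do, and one should be named in advance:
- the ANCOVA form already used for CUDIT-R, with the outcome's own baseline value as covariate; or
- the month-6 group-by-time contrast from a mixed model that explicitly includes baseline and month 6.

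Report the models for months 12 to 30 separately as observational, and say that they do not test the health hypothesis.

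The cost is a change of wording and one more contrast per outcome, with no new data collection.
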